### Study design and setting

TIGER is an international observational cohort study. The duration of the study will approximately be 7 years (2 years inclusion, 5 years follow-up). There are currently 50 participating centers distributed over 18 countries. Centers are located in The Netherlands (10), Sweden (1), Finland (1), Belgium (2), Germany (3), Swiss (1), France (1), Italy (5), Spain (2), United Kingdom (7), Ireland (2), Japan (4), Hong Kong (1), China (1), India (2), United States (5), Canada (1) and Brazil (1). Data from each participating hospital will be collected at the TIGER website (www.tigerstudy.net). Data collection forms can be assessed after login on the website. Each hospital has access to their own dataset.

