### Sample size

The aim is to include 5000 patients. This number suffices for descriptive purposes and clustering of metastases diffusion profiles into meaningful subgroups within predefined strata (patients with adenocarcinoma or squamous cell carcinoma, with and without neoadjuvant therapy, different tumor heights and invasion depths, and following a 2- or 3-field lymphadenectomy). In 2012, the incidence of esophageal cancer was 456.000 new cases worldwide [25]. Only a small percentage of patients with esophageal cancer present with curable disease at time of diagnosis. The aim is to include all 5000 patients with resectable disease in the 50 participating centers in a 2-year time period.

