### Treatment of subjects

#### Staging

Preoperative staging will be performed according to national guidelines. This therefore, may differ per country. Usually, patients are staged with an endoscopy with biopsies, an endoscopic ultrasound, a PET-CT-scan of neck, thorax and abdomen and an ultrasound of the neck. An EBUS-TBNA will be performed if indicated. All patients are discussed in a multidisciplinary team (MDT).

A suspected lymph node is defined as a node larger than > 9 mm short axis or a node 5–9 mm short axis that is round, inhomogeneous and has an irregular border (2 out of 3). In case of PET-CT-scan, pathological nodes are those with FDG uptake, a short axis > 10 mm or those with a short axis between 5 and 9 mm that present with sharp borders.

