#### Neoadjuvant therapy

In case of potentially curative disease (cT1-4a, N0–3, M0) patients may be treated with neoadjuvant therapy, this however, may differ per country and usually consists of chemotherapy or chemoradiotherapy.

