#### Follow-up

Patients will be followed up until 5 years after the operation. Follow-up will usually be scheduled (but differences between countries exist) every 3 months the first year, every 6 months the second until the fourth year and once yearly until the fifth year. Investigations are performed according to national guidelines.

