#### Secondary study parameter(s)

The sensitivity, specificity, and positive and negative predictive values of EUS and PET-CT will be reported. Perioperative morbidity and mortality will be summarized descriptively. For each patient group (squamous cell versus adenocarcinoma, with and without neoadjuvant therapy), explorative cluster analyses will be performed to identify subgroups of patients with different patterns of lymph nodes metastases. Potentially relevant characteristics at the time of surgery like age, gender, tumor location, tumor invasion depth, tumor differentiation, vaso-invasive growth will be included in the analysis. No restrictions will be applied to the number of clusters in each analysis, but the ratio of the largest cluster size to the smallest cluster size should preferably not exceed the value of 3 and/or the smallest cluster size should be minimally 30 patients. Characteristics introducing patient outliers will be excluded and one should further be able to attribute meaning to the resulting cluster profiles. Clusters that show the phenomenon of skip metastases will be noted. The resulting clusters will be evaluated for the diffusion pattern of future metastases during follow-up (descriptive analysis), the number of future metastases during follow-up (Poisson regression or generalized estimation equation, whichever appropriate), for 3- and 5-year overall and disease-free survival (Kaplan-Meier survival analysis). Multivariate analysis will be performed using the Cox hazard regression method. The univariate analysis, including all baseline parameters, will serve as the basis for the multivariate Cox hazard regression model. Variables showing association (*p* < 0.10) with survival in univariate analysis will be included in the multivariate analysis. Age and sex will be included in all multivariate analyses. Results are presented as hazard ratio with exact 95% confidence interval (95% CI). After 5-years of follow-up the efficacy index will be determined (incidence of metastases to an area (%) × 5-year overall survival rate (%)). A log-rank test, Mann-Whitney U test, or χ^2^-test will be used as indicated to compare groups. A value of *p* < 0.05 will be considered statistically significant.

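### Secondary comparisons by neoadjuvant therapy name no center or country term, so they are partly confounded with country, and their p-values are too small where therapy varies mainly between centers

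*Protocol article*

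**What the plan says.** All references are to the protocol article.

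- **Tests.** Secondary study parameter(s): log-rank, Mann-Whitney U or chi-square tests "will be used as indicated to compare groups", followed by "A value of *p* < 0.05 will be considered statistically significant". In their standard form these tests are unstratified and treat patients as independent.
- **Models.** The same section plans a multivariable Cox model with age and sex forced in and other variables chosen by a univariate screen at p < 0.10. Poisson regression or generalized estimating equations (GEE) are options for the number of later metastases, with no cluster unit given. Neither center nor country appears as a stratum, covariate or cluster.
- **Setting.** Study design and setting: "There are currently 50 participating centers distributed over 18 countries".
- **Practice by country.** On neoadjuvant therapy: "this however, may differ per country". On staging: "Preoperative staging will be performed according to national guidelines". On follow-up: "Investigations are performed according to national guidelines", with visit schedules also allowed to vary. The Surgery section says the interval from neoadjuvant therapy to operation may differ by country too.
- **Contrasts by therapy.** Secondary endpoints lists the number of nodes harvested with and without neoadjuvant treatment. The Discussion states the aim of finding out whether neoadjuvant treatment affects the presence and location of nodal metastases.

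**The concern.** The exposure (neoadjuvant therapy) and the way outcomes are produced and measured (staging, timing of surgery, dissection, follow-up imaging) can vary along the same axis, namely country and center. Two separate problems follow.

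1. **Confounding.** A crude comparison of treated and untreated patients partly compares countries: which of them give the therapy, how they dissect and how often they look for recurrence.
2. **Clustering.** Patients of one center resemble each other. Where therapy differs mainly between centers, a test that assumes independent patients understates the standard error, and the p-value is too small.

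The Discussion hopes that radiation fields and the extent of lymphadenectomy can be tailored from the results. An apparent effect of therapy that is really a difference in national practice would therefore matter.

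**Working it through.** **No stated figure to reproduce.** The Sample size section ("The aim is to include 5000 patients") gives no power, effect size or formula, and justifies the number for description and clustering of metastasis patterns. Only the cluster counts can be checked: the listed centers add up to 50 in 18 countries, so the average is 5000/50 = 100 patients per center.

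**Inputs**
- From the article: 5000 patients, 50 centers, significance level 0.05.
- Assumed: a two-sided test (the article does not say), equal center sizes, and an intracluster correlation (ICC) of 0.01 to 0.10. The article gives no ICC.

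**Formula, for therapy constant within center**
- Design effect: DEFF = 1 + (100 − 1) × ICC.
- Actual type I error = 2 × [1 − Φ(1.96/√DEFF)].
- Example at ICC 0.05: DEFF = 1 + 99 × 0.05 = 5.95 and √5.95 = 2.44. Then 1.96/2.44 = 0.80, and the error is 0.422. Effective size is 5000/5.95 = 840.

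**Simulation.** 4000 runs of 50 centers with 100 patients each, a binary outcome with assumed mean 0.4, center rates drawn from a beta distribution with the given ICC, and no true therapy effect. Three allocations were used: therapy constant within center (half the centers each way); half the centers 80% treated and half 20%; and 50% treated in every center.

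| ICC (assumed) | DEFF | Effective N | Formula, constant in center | Simulated, constant | Simulated, 80/20 | Simulated, 50/50 |
|---|---|---|---|---|---|---|
| 0.01 | 1.99 | 2513 | 0.165 | 0.168 | 0.088 | 0.055 |
| 0.02 | 2.98 | 1678 | 0.256 | 0.266 | 0.140 | 0.048 |
| 0.05 | 5.95 | 840 | 0.422 | 0.430 | 0.242 | 0.042 |
| 0.10 | 10.90 | 459 | 0.553 | 0.560 | 0.372 | 0.039 |

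**With the fix.** A center-stratified Cochran-Mantel-Haenszel test on the same data has a type I error of 0.046 to 0.055 in both the 80/20 and the 50/50 patterns. Where therapy is constant within center, that test has no information at all.

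**What this does not measure.** In the simulation, center rates are unrelated to therapy allocation, so the table shows clustering only. Confounding from national practice would come on top, and the article gives nothing from which to size it.

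**The case against.** Several counter-arguments have force.

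- **A reader might infer that therapy is set by country, so that treatment contrasts are simply country contrasts.** The text does not support this. It says only that therapy may differ by country and describes what it usually consists of. The mix within a country or center is not given, so partial confounding is the most that can be claimed.
- **A reader might also infer that all p-values are too small.** That does not hold either. With an even mix inside every center the unstratified test is nominal, or slightly conservative at high ICC. The nodal-pattern clusters that are evaluated for survival and later metastases are formed inside each histology and neoadjuvant group, and can vary between patients of one center. The worst-case design effect does not describe those comparisons.
- **One hundred patients per center pools the two histologies, which the primary analysis keeps separate.** With 50 per center (an even split, assumed), DEFF = 1 + 49 × ICC gives 1.49, 3.45 and 5.90 at ICC 0.01, 0.05 and 0.10, and type I errors of about 11, 29 and 42%. This is smaller but the same in kind.
- **Much is descriptive or already adjusted.** The primary analysis reports counts and percentages, and morbidity and mortality are summarized without tests. Survival has a multivariable Cox model, and GEE is an option for later metastases. All true, but none of these names center or country. If country counted as a baseline variable, it would enter the Cox model only by passing the p < 0.10 screen.
- **The detail may stand in a fuller plan, and the phrase that leaves the choice of test open does not rule out stratified versions.** Fair. But the article does more than stay silent: it names specific tests and a covariate rule, and for the harvested-node comparison it offers no adjusted model.

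**Conclusion.** The point holds in limited form. It concerns secondary contrasts by neoadjuvant therapy: harvested nodes, presence and location of nodal metastases, and any survival comparison by therapy. Run as written, these are partly confounded with country, and their tests are miscalibrated to the extent that therapy varies between centers.

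For an assumed ICC of 0.01 to 0.10, the type I error of a nominal 5% test is about 16 to 55% in the worst of the three patterns (therapy constant within center), about 9 to 37% for an 80/20 versus 20/80 split, and about 5% for a 50/50 mix. These figures rest on the assumed ICC, on 100 patients in every center and, for the simulated patterns, on a binary outcome with mean 0.4. They indicate, rather than measure, what would happen to a rank test on node counts or a log-rank test. Which pattern applies cannot be told from the article. The descriptive summaries have no p-values and are not affected in that respect.

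**What to change.** In Secondary study parameter(s), for the contrasts by neoadjuvant therapy:

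1. Replace the unstratified tests by center- or country-stratified versions, or by regression with a center effect, adjusted for histology, clinical stage and dissection extent.
2. Stratify the Cox models by country and use center-clustered standard errors.
3. Tabulate neoadjuvant therapy by country, so that the reader sees how much of the contrast lies within strata.
4. Where therapy hardly varies within the stratum, report the contrast as descriptive only, without a p-value.

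Steps 1 and 2 have different jobs. Clustered standard errors, or a random effect used only to widen intervals, deal with clustering but do not remove confounding by country. Stratification removes it only where therapy varies inside the stratum, which is why steps 3 and 4 are needed.

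The cost is a little more analysis work, wider intervals and some less favourable p-values. Neither the design nor the sample size has to change.

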## Discussion

The TIGER study is an international observational cohort study, with participation of worldwide renowned esophageal cancer centers, that will investigate the distribution of lymph node metastases is esophageal cancer. This global study group will be a unique international collaboration that will determine the pattern of lymph node metastases in both squamous cell and adenocarcinoma, since, especially in adenocarcinoma, this has not been investigated in multicenter prospective series before [11, 12]. The results of the TIGER study will provide a roadmap of the location of lymph node metastases in relation to tumor histology, tumor location, tumor invasion depth, number of lymph nodes and lymph node metastases, pre-operative diagnostics, neoadjuvant therapy and survival. In addition, it will be investigated whether neoadjuvant chemoradiotherapy and chemotherapy influence the presence and location of lymph node metastases, as some recent reports suggest that lymph nodes can become sterile after neoadjuvant treatment and only fibrosis is found in these lymph nodes [22]. The prognostic value of positive lymph nodes, micrometastases, isolated tumor cells and fibrosis will be investigated. Patient-tailored treatment can be developed on the basis of the TIGER study results, such as the optimal radiation field and the extent of the lymphadenectomy and, additionally, it may aid in the development of a global uniform classification system.

## Trial status

Protocol version 6, date: 08-02-2019

Start recruitment: 03-03-2019

Approximate date recruitment completion: 03-03-2021

## Data Availability

The datasets generated and/or analyzed during the current study will be available from the corresponding author on reasonable request.

## Abbreviations

AJCC: American Joint Committee on Cancer
EBUS-TBNA: Endobronchial ultrasound-transbronchial needle aspiration
EUS: Endoscopic ultrasound
H&E: Hematoxylin and eosin stain
IRB: Investigational Research Board
JES: Japan Esophageal Society
MDT: Multidisciplinary team
PET-CT: Positron emission tomography-computed tomography
